## Abstract

**Background:**

Surgery is the primary treatment for non-small cell lung cancer (NSCLC), but microscopic residual disease may be unavoidable. Preclinical studies have shown that volatile anesthetics might suppress host immunity and promote a pro-malignant environment that supports cancer cell proliferation, migration, and angiogenesis, whereas propofol may preserve cell-mediated immunity and inhibit tumor angiogenesis. However, clinical evidence that propofol-based total intravenous anesthesia (TIVA) can reduce tumor recurrence after curative resection remains inconsistent due to the retrospective observational nature of previous studies. Therefore, we will test the hypothesis that the recurrence-free survival (RFS) after curative resection of NSCLC is higher in patients who received TIVA than volatile anesthetics (GAS) in this multicenter randomized trial.

**Methods:**

This double-blind, randomized trial will enroll patients at 22 international sites, subject to study registration, institutional review board approval, and patient written informed consent. Eligible patients are adult patients undergoing lung resection surgery with curative intent for NSCLC. Exclusion criteria will be contraindications to study drugs, American Society of Anesthesiologists physical status IV or higher, or preexisting distant metastasis or malignant tumor in other organs. At each study site, enrolled subjects will be randomly allocated into the TIVA and GAS groups with a 1:1 ratio. This pragmatic trial does not standardize any aspect of patient care. However, potential confounders will be balanced between the study arms. The primary outcome will be RFS. Secondary outcomes will be overall survival and complications within postoperative 7 days. Enrollment of 5384 patients will provide 80% power to detect a 3% treatment effect (hazard ratio of 0.83) at alpha 0.05 for RFS at 3 years.

**Discussion:**

Confirmation of the study hypothesis would demonstrate that a relatively minor and low-cost alteration in anesthetic management has the potential to reduce cancer recurrence risk in NSCLC, an ultimately fatal complication. Rejection of the hypothesis would end the ongoing debate about the relationship between cancer recurrence and anesthetic management.

**Trial registration:**

The study protocol was prospectively registered at the Clinical trials (https://clinicaltrials.gov, NCT06330038, principal investigator: [name]; date of first public release: March 25, 2024) before the recruitment of the first participant.

## Background

Lung cancer is the second most diagnosed cancer worldwide and the leading cause of cancer death in men and women combined (Sung et al. 2021). Non-small cell lung cancer (NSCLC) accounts for 80–85% of the total global lung cancer burden (Thai et al. 2021). The standard treatment for stage I, II, and some stage IIIA NSCLC is surgical resection. Despite advances in radiotherapy, chemotherapy, and molecular targeted and immunotherapy, 30–75% of NSCLC patients who undergo curative surgery develop recurrence, which carries a high risk of mortality (Taylor et al. 2012; Yun et al. 2022).

Even with the best technique, a fraction of cancer cells might remain due to incomplete resection margins or iatrogenic “seeding” of tumor cells into the lymphatic and blood streams with surgical manipulation. Some patients may already harbor micrometastases and scattered tumor cells at the time of surgery (Denis et al. 1997; Eschwege et al. 1995; Foss et al. 1966; Hiller et al. 2018a; Horowitz et al. 2015; Vona et al. 2000). Whether this minimal residual disease leads to clinical metastases depends largely on the balance between the ability of the tumor to seed, proliferate, and promote angiogenesis and the activity of anti-metastatic immunity as a host defense (Holmgren et al. 1995; Shakhar and Ben-Eliyahu 2003; Smyth et al. 2001).

There is growing evidence that perioperative factors play a critical role in promoting cancer recurrence and metastasis (Horowitz et al. 2015), and that the anesthetic modality used during surgery can have a significant impact on residual or circulating tumor cells, and the patient’s immune response (Bar-Yosef et al. 2001; Hiller et al. 2018a; Kim and Reviews 2017; Sacerdote et al. 2000; Schlagenhauff et al. 2000; Wall et al. 2019; Yeager et al. 1995).

Anesthetics have the potential to impair numerous components of the host response in animal studies, including neutrophil, macrophage, dendritic cell, T cell, and NK-cell functions (Brand et al. 1997; Markovic et al. 1993; Melamed et al. 2003; Shapiro et al. 1981).

However, anesthetic medication types may have disparate effects on cancer recurrence (Melamed et al. 2003). Preclinical and biomarker studies have shown that volatile anesthetics might promote immunosuppression and create a pro-malignant environment including upregulation of hypoxia-inducible factor that supports cancer cell proliferation, migration, and angiogenesis, whereas propofol may preserve cell-mediated immunity and inhibit tumor angiogenesis (Buckley et al. 2014; Cho et al. 2017; Hiller et al. 2018a; Hiller et al. 2018a; Iwasaki et al. 2016; Jaura et al. 2014; Kim and Reviews 2017; Looney et al. 2010; Markovic-Bozic et al. 2016; Melamed et al. 2003; Tavare et al. 2012; Wall et al. 2019).

Despite the availability of biologically plausible explanations, clinical evidence that propofol-based total intravenous anesthesia (TIVA) can reduce tumor recurrence after curative resection remains inconsistent (Chang et al. 2021; Enlund et al. 2022; Hasselager et al. 2021; Hovaguimian et al. 2021; Jun et al. 2017; Lai et al. 2019; Lee et al. 2016; Makito et al. 2020; Wigmore and Farquhar-Smith 2016; Yoo et al. 2019; Yoon et al. 2022; Zheng et al. 2018), mainly because previously conducted studies have been retrospective or observational in nature. Given the risk of residual confounding inherent in observational studies, randomized trials are required to evaluate the influence of anesthetics on oncologic outcomes.

In this multinational, multicenter clinical trial, we will test the hypothesis that local or metastatic recurrence after curative resection of NSCLC is lower in patients randomized to propofol-based total intravenous anesthesia (TIVA group) than in patients randomized to volatile anesthesia (GAS group). Secondary hypotheses are that overall survival (OS) is increased when patients receive TIVA rather than GAS anesthesia and that postoperative complication rates are not different between the TIVA and GAS anesthesia groups.

In this report, we outline our approach and study protocol to establish an a priori record of the proposed study methods and endpoints.

## Methods

### Study design

This pragmatic, randomized, double-blind, multicenter, and multinational study will be approved by the Regional Ethics Committee in 22 international sites, and informed consent will be obtained from all participants. The steering committee of the study developed the protocol and will manage the conduct of the trial, and obtain and manage study data. The study is coordinated by the Samsung Medical Center (SMC), Sungkyunkwan University, Seoul, Korea, and is registered at ClinicalTrials.gov (#NCT06330038). This clinical trial will be investigator-initiated and non-commercial. The trial will be done in accordance with Good Clinical Practice guidelines, the principles of the Declaration of Helsinki, and relevant regulatory requirements.

### Outcomes

#### Primary and secondary outcomes

The primary outcome of this study is recurrence-free survival (RFS) after curative resection of NSCLC. The observed time-to-recurrence is defined as the duration from the date of surgery to the earliest date between the recurrence/metastasis date and the last follow-up date due to death from any cause, any uncontrollable factor during the study, or the end of the study.

Secondary survival outcomes are locoregional RFS (LRFS), metastasis-free survival (MFS), overall survival (OS), and cancer-specific survival (CSS). The observed time-to-events for LRFS and MFS are defined similarly to that of RFS. The observed time-to-event for OS is defined as the duration from the date of surgery to the earliest date among the date of all-cause death and the last follow-up date due to any uncontrollable factor during the study, or the end of the study. The observed time-to-event for CSS is defined as the duration from the date of surgery to the earliest date among the date of cancer-specific death, and the last follow-up date due to death from any cause other than cancer-specific death, any uncontrollable factor during the study, or the end of the study. Other secondary outcomes are postoperative complications. The postoperative complication is a composite outcome defined as any complication occurring within 7 days post-surgery or at discharge if earlier. The applicable complications are defined by the Society of Thoracic Surgeons (STS) general thoracic surgery databases (Crabtree et al. 2018), and the Clavien-Dindo classification (Wong, Oliver, and Moonesinghe 2017). The postoperative complication is a reasonable surrogate for an immediate postoperative outcome, which we believe will be similar between study groups based on Pasin et al.’s meta-analysis of short-term mortality after propofol vs. volatile anesthesia (95 studies, *n* = 9806 total patients) (Pasin et al. 2015).

#### Safety outcomes

The anesthetics used in this study are routinely administered during general anesthesia and comprise the vast majority of general anesthetics used worldwide. Therefore, our study design does not increase risk compared to standard anesthesia practice except for the risk of randomization. We do not expect any obvious safety outcomes that we believe are due to the intervention.

### Setting and population

We plan a randomized controlled trial at 22 international sites (hospitals in Korea, the USA, Thailand, China, the UK, and India). Screening can be performed either in the outpatient unit or in the ward. The main investigator at each participating site will be responsible for the screening of all adult patients who are scheduled for elective lung resection surgery with curative intent for NSCLC. A screening log will be compiled and will include all screened patients, irrespective of whether or not they are eligible for inclusion. Patients who meet all study criteria will be contacted by the main investigator to obtain written informed consent. A total of 5384 subjects will be enrolled from multiple study sites. Adult patients scheduled for curative resection of NSCLC will be randomized to either the TIVA or GAS group (Fig. 1).

**Fig. 1 Fig1:**
[figure not shown]
The Consolidated Standards of Reporting Trials flow diagram. TIVA; total intravenous anesthesia, GAS; inhalational anesthesia

Our inclusion criteria are (1) age 19 years old or older, (2) American Society of Anesthesiologists physical status (ASA) I‒III, (3) The Eastern Cooperative Oncology Group (ECOG) performance status 0–2, (4) Lung resection surgery (segmentectomy, lobectomy, bilobectomy, pneumonectomy; video-assisted, robot-assisted, or open) with curative intent for NSCLC (clinical Tumor, Node, Metastasis (TNM) stage I–IIIA).

Exclusion criteria will be (1) distant metastasis or malignant tumor in other organs as manifested in diagnostic tests such as CT or PET scan, and not in long-term remission according to the attending surgeon, (2) severe neurologic conditions, (3) severe hepatic disease (Child–Pugh classification C), (4) renal failure requiring renal replacement therapy, (5) history of anesthesia and/or surgery within 1 year, (6) previous surgery due to lung cancer (except diagnostic biopsies), (7) contraindications to any study medication (history of allergy, hypersensitivity reaction, or any other contraindication), (8) planned joint extrapulmonary procedure, (9) surgery under cardiopulmonary bypass or extracorporeal membrane oxygenation, (10) planned postoperative sedation, (11) pregnancy, or lactation, (12) patient refusal.

Criteria for exit (drop out) from the trial are (1) patient withdrawal and (2) surgery cancelation. A Consolidated Standards of Reporting Trials (CONSORT) flow diagram will reveal the flow of study participants (Fig. 1).

### Randomization

A stratified block randomization with a block size of 4 will be used to allocate subjects into two intervention groups (TIVA and GAS) with a 1:1 ratio. A computer-generated assignment sequence will be stratified according to the participating site and clinical cancer stage, using a web-based automated randomization system (www.gastiva.org). This system is centralized, password-protected, and encrypted. At each participating site, random allocation will be done according to the assignment sequence before induction of anesthesia.

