### Blinding

The group designation will be blinded to the following individuals: (1) patients: patients will not be informed of the randomization assignment and will receive general anesthesia during the intervention, (2) surgeons: the anesthesia process will be initiated prior to the surgeon’s entry into the operating room. This is followed by the placement of opaque drapes that effectively prevent the surgeon from observing any details of the anesthesia technique. The opaque drapes remain in place from the induction of anesthesia throughout the entire surgical procedure, (3) attending anesthesiologists: anesthesiologists in the operating room cannot be blinded to randomization assignment but are not involved in the study enrollment or assessment of the results, (4) each site will have at least two participating investigators (main investigator and outcome assessor). The main investigator will be entering patient information into an electronic case report form (eCRF), being aware of the allocated group, and collecting intraoperative data. The outcome assessor will remain blinded to the allocated group and evaluate the postoperative outcomes. All data will be uploaded on web-based eCRF of www.gastiva.org and group allocation will be opened only when all the collected data are ready for statistical analysis.

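### One published block size of 4 within site-by-stage strata, with a main investigator who recruits and knows allocations, makes upcoming allocations partly predictable

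*Protocol article*

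**What the plan says.** All of this is in the protocol article.

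- **Randomization:** "A stratified block randomization with a block size of 4 will be used to allocate subjects into two intervention groups". The ratio is 1:1 and the sequence is "stratified according to the participating site and clinical cancer stage, using a web-based automated randomization system". On concealment: "This system is centralized, password-protected, and encrypted". On timing: "random allocation will be done according to the assignment sequence before induction of anesthesia".
- **Setting and population:** "The main investigator at each participating site will be responsible for the screening of all adult patients" scheduled for the surgery, and "Patients who meet all study criteria will be contacted by the main investigator to obtain written informed consent". A log is kept of everyone screened.
- **Blinding:** "The main investigator will be entering patient information into an electronic case report form (eCRF), being aware of the allocated group". The same person collects the intraoperative data. Attending anesthesiologists, who also know the group, are kept out of enrollment. No such separation is stated for the main investigator. Each site also has an outcome assessor who stays blinded.

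**The concern.** Allocation concealment requires that whoever decides whom to approach, and when, cannot foresee the next assignment. Here one role per site controls recruitment, sees past assignments and knows each patient's stratum, and the article publishes the only block size. In a balanced block of 4 the later assignments are constrained by the earlier ones, so a running count within a stage at one site reveals some of what comes next. The encrypted system protects the list but does not prevent this deduction.

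At stake is the comparability of the arms. The trial is sized for a 3-point difference in 3-year recurrence (20% against 17%, hazard ratio 0.83), so a modest prognostic imbalance would matter. Because allocation follows consent, the exposed decisions are mainly whether to approach a patient and when to schedule the case.

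**Working it through.** **Inputs.** Block size 4, ratio 1:1, strata of site by clinical stage (Randomization); 5,384 enrolled (Sample-size calculations); 22 sites (Setting and population). The article gives no predictability figure to reproduce. Its enrolled number does reproduce: 4,845 / 0.90 = 5,383.3, rounded up to 5,384. The sample size itself is not affected by this point.

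**Step 1. Certain allocations when all earlier patients are already allocated.** There are six balanced blocks (AABB, ABAB, ABBA and their mirror images), so 6 × 4 = 24 positions.
- Position 4 is always forced: 6 positions.
- Position 3 is forced when the first two match (AABB, BBAA): 2 positions.
- Total 8/24 = 33.3%. Applied to the trial, 5,384 / 3 ≈ 1,795, less a small loss from incomplete final blocks.

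**Step 2. Best guess (name the arm that is behind; toss a coin when level).**
- Position 1: 0.5
- Position 2: 2/3
- Position 3: 1/3 × 1 + 2/3 × 0.5 = 2/3
- Position 4: 1
- Mean: (0.5 + 0.667 + 0.667 + 1) / 4 = 17/24 = 70.8%

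**Step 3. Allowing for patients still awaiting allocation.** Screening may take place in the outpatient unit or on the ward, while allocation is made just before induction, so earlier patients in the stratum may still be unallocated when the next is approached. Let k be their number. The article does not give the interval between consent and allocation, so k is an assumption and a range is shown.

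| k | Certain | Best guess right |
|---|---|---|
| 0 | 33.3% | 70.8% |
| 1 | 8.3% | 58.3% |
| 2 | 0% | 54.2% |
| 3 | 0% | 50% |

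For k = 1, only position 4 can be certain, and only when positions 1 and 2 match: (1/3) / 4 = 8.3%. The best guess is (0.5 + 0.5 + 2/3 + 2/3) / 4 = 58.3%. For k = 2, only position 4 gains anything, from knowledge of position 1: (0.5 + 0.5 + 0.5 + 2/3) / 4 = 54.2%.

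**Step 4. Effect of varying the block size (k = 0).** This was simulated with 3,000 sequences of 60 allocations. The guesser updates on past allocations and is assumed to know the set of sizes but not their order.

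| Design | Certain | Best guess right |
|---|---|---|
| Fixed 4 | 33.3% | 70.8% |
| Random 4/6 | 5.5% | 69.0% |
| Random 4/6/8 | 2.4% | 67.8% |
| Recruiter unaware of past allocations | 0% | 50% |

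The fixed-4 row is the exact result; the simulation agreed with it (33.3% and 70.9%).

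**The case against.** The strongest reply is that a reader might infer that about 1,795 allocations will be known in advance. The article does not support that. The figure is a ceiling that holds only at k = 0. Recruitment is expected to be concentrated: at the 4:3:3 ratio given in the text, about 2,154 patients (0.4 × 5,384) come from one named center and 1,615 (0.3 × 5,384) from another. Several consented patients in a stratum could be waiting there at once, and Step 3 shows how fast predictability then falls. This stands. Small sites and rarer stages may still sit near k = 0, and rescheduling could exploit a known next slot even in busy strata.

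A reader might also infer that selection bias is present and beyond repair. That goes too far. Bias also needs a recruiter who tracks strata and selects on prognosis, and nothing in the article suggests this. Clinical stage is a stratification factor, so selecting by stage cannot unbalance the arms beyond incomplete blocks. The multivariable Cox model adjusts for age, tumor size and many other factors, and the screening log allows selective approach to be checked. These limits stand. They do not reach unmeasured prognosis, and the log-rank test and univariable Cox model listed first for the primary outcome are unadjusted.

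Two defenses do not hold. The central system answers access to the list, not inference from past allocations. The Blinding section's statement that allocation is opened only once data are ready for analysis cannot cover the main investigator, whom the same section describes as aware of the group.

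**Conclusion.** The point holds as partial predictability. The article itself states the single block size and gives recruitment and knowledge of allocations to one role, so this is a stated choice and not a detail left to a fuller document. Depending on how many earlier patients in a stratum await allocation, between 0% and 33.3% of allocations are certain to someone who counts, and best-guess accuracy lies between 50% and 70.8%. The upper ends assume that every earlier allocation in the stratum is known, and that the investigator keeps count by stage.

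This is an avoidable opportunity for selection bias in whom to approach or when to schedule. Existing features limit it, but selection on unmeasured prognosis could not be fully removed by analysis. Stratifying by site and stage is not itself an error. The change is worth making but does not call the trial into question.

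**What to change.** 1. For future allocations, set the web system to randomly varying block sizes, for example 4, 6 and 8, with sizes and order not disclosed to sites. This removes most certain predictions (33.3% to about 2%) but little of the best-guess advantage (70.8% to about 68%). Removing the number 4 from site documents without changing the system would achieve little, because the article has published it.
2. Where existing site roles allow, have screening and consent done by someone unaware of past allocations. This is the stronger part, since it returns guessing to 50%. The Blinding section already provides a second, blinded investigator at each site.

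Cost: the first part needs a system setting and a protocol sentence; the second needs some reassignment of roles across 22 sites. The largest possible end-of-stratum imbalance rises from 2 to 4 patients. If there are three stage strata per site (an assumption; the number is not stated), that is 22 × 3 = 66 strata. Even if all were off by 4 in the same direction, the imbalance would be 264 of 5,384 (4.9%), an information loss of 0.049² ≈ 0.24%, which is negligible. Sample size, endpoint and clinical care are unchanged.

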### Blinding

The group designation will be blinded to the following individuals: (1) patients: patients will not be informed of the randomization assignment and will receive general anesthesia during the intervention, (2) surgeons: the anesthesia process will be initiated prior to the surgeon’s entry into the operating room. This is followed by the placement of opaque drapes that effectively prevent the surgeon from observing any details of the anesthesia technique. The opaque drapes remain in place from the induction of anesthesia throughout the entire surgical procedure, (3) attending anesthesiologists: anesthesiologists in the operating room cannot be blinded to randomization assignment but are not involved in the study enrollment or assessment of the results, (4) each site will have at least two participating investigators (main investigator and outcome assessor). The main investigator will be entering patient information into an electronic case report form (eCRF), being aware of the allocated group, and collecting intraoperative data. The outcome assessor will remain blinded to the allocated group and evaluate the postoperative outcomes. All data will be uploaded on web-based eCRF of www.gastiva.org and group allocation will be opened only when all the collected data are ready for statistical analysis.

